## Abstract

**Background:**

University students’ mental health problems are prevalent globally, which underlines the need for accessible and cost-effective mental health services in universities. Loneliness is a key risk factor for mental health problems, and it disproportionately affects students from minority backgrounds. Therefore, addressing loneliness and fostering inclusion and equality can be crucial strategies for enhancing students’ well-being.

**Objective:**

The aim of this study is to investigate a social-identity group intervention called Groups 4 Health (G4H) for university students’ well-being using both quantitative and qualitative methods. Here, we present the research protocol and report preliminary descriptive findings from the study cohort.

**Methods:**

The quantitative part of the study is a 4 parallel-arm nonrandomized controlled trial aiming to recruit 600 student participants from the University of Helsinki. The experimental group, which receives the G4H intervention, includes 5 group meetings held over a 7-week period. The experimental group will be compared with 2 active comparators: groups organized by the University of Helsinki study psychologists and a 7-week online intervention course focused on well-being and study skills, and to a no-intervention control group. The primary quantitative outcomes of the study are loneliness and depression; secondary outcomes include several measures of students’ well-being, academic performance, and cost-effectiveness of the intervention. Quantitative data are collected before the intervention, during the intervention (at week 3), immediately post intervention (at week 7 after baseline), and at 1- and 3-month follow-ups. The qualitative part of the study explores the challenges and opportunities related to inclusion and equality identified in the G4H intervention using observations, interviews, and focus group discussions.

**Results:**

In the preliminary findings based on the first data freeze in March 2025, we observed differences in the background characteristics between the trial arms, highlighting the need to address group selection bias. First results from the study are expected in 2026.

**Conclusions:**

If proven effective, these interventions have significant potential to improve students’ well-being in both short and long term, fostering mental health and supporting academic success and future career paths.

## Introduction

### Background

University students’ mental health problems are highly prevalent globally [1]. In Finland, 36% of university students reported high levels of psychological distress and 24% reported increased loneliness in the *2021 Finnish Student Health and Well-Being Survey* [2]. Anxiety and depressive symptoms at the start of university studies are often persistent and related to poorer academic performance and lower engagement [3]. The need for accessible, cost-effective mental health services in universities is substantial [4].

Loneliness (the discrepancy between one’s actual and desired social relationships) has been recognized as one of the key risk factors for numerous adverse psychological and somatic health outcomes among students and youth [5] and in various population-based samples [6,7].

Having positive relationships and feeling socially connected is also essential for academic performance. Loneliness, social isolation, and low social status impact intellectual achievement [8], whereas engaging in the academic environment reinforces individuals’ learning activities [9].

Mental health problems are more prevalent among many minority groups, who experience psychological symptoms more often than the rest of the population [10-12]. Several studies have also found that belonging to more than one minority group increases the risk of stressful life situations, mental health problems, and thus the need to use mental health services [13,14]. Belonging to minorities may also increase the risk of social isolation. According to the School Health Promotion study [12], young people belonging to gender and sexual minorities show elevated levels of loneliness, exclusion, and difficulties in receiving help in Finland. In addition, young people with immigrant backgrounds and young people with disabilities face considerable risks of loneliness [15]. These difficulties are largely caused by minority stress, which in turn has been linked with experiences of discrimination and unequal treatment [12,16].

With this background, interventions targeting loneliness and supporting social connectedness, inclusion, and equality could be a significant way to approach the student mental health crisis. The Groups 4 Health (G4H) intervention studied in this protocol aims at improving well-being by supporting individuals’ social group memberships that are compatible with their social identity [17].

G4H builds on the social identity approach to health (SIAH) [18,19] and the social identity model of identity change (SIMIC) [20,21]. The SIAH [18,19] comprises 2 related theories, the social identity theory [22] and self-categorization theory [23], claiming that individuals’ internalized group memberships have a significant role in their sense of self and that shared identities are important for productive social interaction. Therefore, belonging to multiple social groups that align with the individual’s identity is crucial for a sense of purpose and belonging, as well as for receiving support from others [18]. The role of group memberships is further emphasized during transitional life events such as moving to another country or entering a university, which may be stressful and may also affect an individual’s access to their social groups. The SIMIC further states that during stressful and transitional life situations, well-being can be enhanced by both managing and strengthening the individual’s social group memberships before the life change (the social identity continuity pathway) and by becoming a member of new social groups that align with the individual’s identity (the social identity gain pathway) [20,21].

The fact that G4H addresses major life changes and social identities makes it particularly relevant in the university context. Many students experience major changes, such as relocating to a new country or city, integrating into new communities, and leaving familiar ones behind. For minority students, finding new social groups that align with their identity can be even more challenging, emphasizing their need for support.

This protocol provides a unique opportunity to study the G4H in the university context with a multimethod approach that integrates both quantitative and qualitative methods. By implementing this approach, we aim to capture not only the effectiveness of the G4H intervention and the participant- or facilitator-related factors that moderate the effectiveness, but also the perspectives of minority students participating in the intervention, which is an aspect that has been overlooked in previous research. The inclusion of qualitative methods is crucial, as it allows us to gain deeper insights into the experiences and potential challenges faced by these students, enriching our understanding of the intervention’s impact.

Additionally, neither the cost-effectiveness of the intervention nor its effectiveness on academic performance has been explored in previous studies. Both of these analyses are essential for assessing its suitability and adaptability in promoting student well-being. Furthermore, to our knowledge, the effectiveness of the G4H has been assessed only in Australia in studies organized by the developers of the intervention. These represent clear gaps in the existing literature that this protocol aims to address.

### Aim and Objectives

The aim of this study is to investigate the effectiveness of the G4H intervention for university students’ well-being using both quantitative and qualitative methods. Our study includes 2 active comparators: intervention groups facilitated by the University of Helsinki (UH) study psychologists and an online intervention course focused on well-being and study skills. A control group of students who are not participating in any active well-being services at UH is also included.

Our first objective is to investigate the effectiveness and cost-effectiveness of the G4H intervention in (1) supporting well-being (most importantly by reducing loneliness and depression) and (2) supporting academic performance among university students. The second objective is to explore which factors moderate or mediate the effectiveness of the interventions. The third objective is to focus on the G4H intervention’s inclusiveness and the capacity of the G4H intervention to promote equality via qualitative methods.

Our research questions (RQs) are as follows:

RQ1: How effective is the G4H intervention in reducing loneliness and depression and in supporting university students’ well-being compared with the 2 active comparators and the control group? (objective 1)RQ2: Does the G4H intervention support academic performance compared with the active comparators and the control group? (objective 1)RQ3: Is G4H cost-effective compared with the 2 active comparators and the control group? (objective 1)RQ4: How do factors related to the participant, facilitator, or intervention fidelity mediate or moderate the effectiveness of the intervention? (objective 2)RQ5: What are the challenges and opportunities related to inclusion and equality in the G4H intervention? (objective 3)

Compared with the no-intervention control group, we hypothesize that all active interventions reduce students’ loneliness and depression (RQ1) and improve students’ academic performance (RQ2). However, participants in the G4H intervention will experience a more long-term reduction in loneliness than those in the other active intervention groups [24]. We hypothesize that treatment alliance [25,26] and higher fidelity to the G4H manual mediate the interventions’ outcomes (RQ4). Regarding facilitators’ characteristics, we hypothesize that their greater self-rated skills and enjoyment in therapeutic work as well as agreeableness, openness, and engagement in personality traits and interpersonal relating will be positively associated with treatment alliances and intervention outcomes; and, conversely, greater difficulties and negative feelings in therapy work will be negatively associated with treatment alliances and outcomes [27-29]. Regarding motivation (RQ4), we set our hypotheses based on the self-determination theory [30] and the integral model of treatment motivation [31]. We hypothesize that autonomous motivation to participate in the intervention predicts greater engagement and increased effectiveness, whereas controlled motivation predicts lower engagement and effectiveness. We further hypothesize that engagement partially mediates the relationship between motivation and intervention effectiveness. No preliminary hypotheses are posed regarding RQs 3 and 5.

## Methods

### Trial Design

We conduct a parallel arm nonrandomized controlled trial with a 1:1 allocation ratio. We compare 3 intervention arms to a no-intervention control group as follows:

Arm 1: The experimental group, G4H.Arm 2: Active comparator group 1, the study psychologists’ group interventions (SPGs)Arm 3: Active comparator group 2, toward better well-being and studying intervention (TBWS).Arm 4: No-intervention control group.

The study design and timeline are presented in Figure 1. The study follows the Standard Protocol Items: Recommendations for Interventional Trials (SPIRIT) guidelines.

**Figure 1. F1:**
[figure not shown]
Trial arms, intervention schedule, and points of assessment. The dashed vertical lines indicate points of assessment. A circle with a dashed outline indicates an optional meeting. △: online meeting; ○: live or online meeting; X: Groups 4 Health facilitators’ assessments.

### Interventions

#### Overview

The interventions in each active trial arm represent courses provided by UH for students who are seeking help to improve their overall well-being and study skills. Additionally, a control group consisting of students receiving no intervention is included. Participation in the study and in the interventions is voluntary, and participants can withdraw from participating at any point without any negative consequences.

#### Arm 1: G4H (The Experimental Group)

G4H is a manualized group intervention that targets social group memberships with the aim of improving well-being [17], as discussed in the introduction.

The G4H intervention consists of five 90-minute sessions that aim to provide participants with the knowledge and skills they need to effectively manage their social group memberships and identities. Each of the 5 intervention sessions pertains to 1 module. Each module integrates exercises and discussions from the G4H workbook targeting various aspects of group dynamics as outlined in the SIAH and SIMIC frameworks. In brief, the first module “schooling” provides psychoeducation about the importance of social group memberships for health; the second module “scoping” supports the participants in exploring their social identities and networks; the third module “sourcing” aims at strengthening the social identities that are valued by the participant; the fourth module “scaffolding” supports making a social action plan to establish new valued group memberships; and finally, the fifth module “sustaining” aims at revisiting the intervention, discussing any potential difficulties, and encouraging the maintenance of group memberships [17]. A detailed description of the modules can be found in the G4H manual [32].

At the UH, the G4H group size can vary between 4 and 9 university students. The groups are mostly organized face-to-face, although some groups meet entirely remotely. The students earn 2 European Credit Transfer and Accumulation System (ECTS) credits for completing the G4H intervention.

G4H groups at the UH are facilitated by 2 psychology students carefully trained for the intervention and mentored by experienced clinical psychologists. Psychology students interested in facilitating the G4H intervention can sign up for G4H facilitator training. During the 2-month training course, facilitators are introduced to the intervention literature (approximately 15 h) and attend lectures on the background theory, structure, and content of the intervention (approximately 6 h). In the more practical part of the training, the facilitators practice how to deliver the intervention and gain first-hand experience of participating in the intervention by conducting the intervention with each other. Finally, after the practice meetings, each pair facilitates one 5-session G4H intervention for a group of UH students. Additional reflection meetings are held with a clinically experienced psychologist ([name]), where the facilitators share their experiences and any problems or questions they may have encountered. During the training, facilitators keep a learning diary, which supports further introspection and reflection. The student facilitators earn 2.5 ECTS credits for completing the intervention training.

The effectiveness of G4H has been studied earlier in Australia. In a nonrandomized controlled study, G4H (n=83) significantly improved well-being and social connectedness of young adults after the intervention and in 6-month follow-up relative to the control group (n=75). In a randomized controlled trial by Haslam and colleagues [33], G4H (n=66) decreased loneliness and social anxiety and increased group memberships significantly more than treatment as usual (n=54) [17]. In a randomized noninferiority trial by Cruwys and colleagues [24], G4H (n=84) was compared with cognitive behavioral therapy (CBT; n=90). Both interventions were equally effective in reducing loneliness by the end of the intervention period. However, the G4H group demonstrated a maintained reduction in loneliness during the follow-up. Both interventions significantly reduced depressive symptoms, with no significant differences between G4H and CBT [24]. In all 3 controlled studies on the effects of G4H, the inclusion criteria were low mood and loneliness.

#### Arm 2: SPGs (Active Comparator 1)

The UH study psychology team organizes group interventions for various challenges related to studying for bachelor’s and master’s students. The SPGs offer client-centered peer support facilitated mostly by 2 study psychologists (some individual sessions may have only 1 facilitator). The recurring themes in the SPGs include challenges with attention, independent studying, scientific writing, and support for re-entering the studies after a break. The structure of the different thematic groups is similar—short presentations, group discussions, practices, and homework. These groups are implemented mostly as face-to-face meetings; however, in some groups, part of the meetings are conducted face-to-face and part as remote meetings. One group typically lasts for a study period and comprises five to six 90‐105 minute sessions. The typical group size ranges from 10 to 12 students. The interventions have potential in supporting study skills and the challenges of initiating study tasks, identifying and normalizing unpleasant thoughts and emotions related to studying, and acknowledging the role of one’s individual situation and well-being in study planning. The study psychologists’ work is bound by the legal and ethical requirements for licensed psychologists in Finland, overseen by the National Supervisory Authority for Welfare and Health (Valvira).

#### Arm 3: TBWS (Active Comparator 2)

TBWS is an optional, 7-week online intervention course available for all UH students that aims to foster well-being and study skills. The course protocol has been described in detail earlier by Asikainen and Katajavuori [34]. The course is based on the principles of acceptance and commitment therapy [35] and aims to promote psychological flexibility. In addition, it aims to support study skills such as time management. The course takes place on an online learning platform (Moodle), and the students earn 3 ECTS credits for completing it. This course progresses weekly and has 6 central themes, including an introduction to the themes, individual work in practicing psychological flexibility and study skills, and weekly peer group discussions. The peer group work is an important part of the intervention and lasts throughout the course. In the peer groups, there are about 5 students in each group, and the groups remain the same throughout the course. Acceptance and commitment therapy–based interventions have been shown to support well-being among university students [36], and previous studies have suggested that this course can improve students’ well-being and studying in several ways [37,38]. Thus, participating students have the potential to benefit from this intervention in terms of increased well-being.

#### Arm 4: The No-Intervention Control Group

The control group consists of students who are currently not taking part in any group interventions for study skills or psychological well-being at the UH. The participants in the control group may, however, take part in other social and mental health services than those provided by the UH, and this is not restricted during their participation in the study. The recruitment and data collection among the control group are scheduled to take place simultaneously with the active intervention groups: the participants are recruited at the same time, and they answer the questionnaires at the same pace as the active interventions progress during the academic year.

The interventions studied in this protocol have been developed for educational contexts and thus are expected to be well-suited for the university context. As discussed earlier, the G4H builds on SIAH and SIMIC, particularly aiming at supporting well-being during transitions in life, such as entering a university [21]. In addition, both the SPGs and the TBWS courses have been specifically developed by experts within the UH for supporting university students’ well-being and academic ability.

### Participants

#### Setting and Timeline

The study is conducted in an academic setting among UH students in Finland. The recruitment has progressed as follows: for the RQ1-RQ3, the recruitment for the first data freeze ended at the end of 2024, and for RQ5, the recruitment ends by the end of the year 2025. For the more explorative objective 2 (RQ4) on the factors that mediate or moderate intervention effectiveness, we assume that a larger sample is required, and recruitment continues longer (current ethical approval allows data collection until the end of 2028). We completed the first data freeze in March 2025 for the RQ1 to RQ3 and will complete the data collection of the qualitative data for the RQ5 by December 2026.

The quantitative data collection started in March 2022 for the G4H and the SPGs. From October 2022, the data collection from all 3 interventions and the no-intervention control group has taken place simultaneously. The intervention schedule and points of assessment are illustrated in Figure 1. It should be noted that data on health care and social service use, as well as the participants’ minority status and readiness to attend the intervention, were gathered only from students who participated starting from March 2023 for the no-intervention control group and from September 2023 for the active intervention arms. The research ethics committee was informed about these added outcome measures, and a new ethical approval was obtained from the committee before data collection started.

In the collection of qualitative data, participant observation is conducted in the meetings of the G4H group and interviews with facilitators (n=9) and intervention participants (n=11) at the end of the intervention period. In addition, the follow-up interviews with intervention participants will be conducted 12 months after the first interview (2024‐2026). Additionally, focus groups with young people belonging to minorities (n=19 participants) are arranged to discuss G4H in terms of equality and inclusion during the data collection period (2023‐2025).

#### Sample Size

For RQ1-RQ3, the target minimum sample for the quantitative study is 600 participants, distributed evenly across 4 groups (150 participants per group). Since comparable previous studies with a similar group of participants using the same outcome measures are not available, it was not possible to make exact a priori sample size calculations. However, based on an estimation with the G*Power software (version 3.1) [39] on a repeated measures analysis of variance design with between-groups factors, this target sample size would yield at least 95% power for the detection of small effect sizes (*f*=0.20) as defined by Cohen [40] when considering multiple comparisons and a 35% attrition rate. Previous studies with different designs investigating the G4H intervention have demonstrated significant treatment effects with smaller samples ranging from 66 [33] to 84 [24] participants in the G4H group, supporting the expectation that our larger sample will be sufficient to detect meaningful treatment effects, or lack thereof.

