**Figure 2. F2:**
[figure not shown]
Study recruitment flow chart. Duplicate participants had already participated in the study (either in the same trial arm or in another arm). Controls: no-intervention control group; G4H: Groups 4 Health; SPG: study psychologists’ group interventions; TBWS: toward better well-being and studying intervention; UH: University of Helsinki.

A high proportion of the university students enrolled in the interventions decided to participate in the study. The minimum target sample size (n=150) was attained for the G4H (n=155), TBWS (n=216), and control group (n=203). For the SPGs, the target sample size was not attained (n=125).

The anticipated study completion date for all data collection is by the end of the year 2028. Analyses for RQ1 and RQ3 are anticipated to take place in years 2025 and 2026, analyses for RQ2 in years 2026 to 2027, and analyses for RQ4 and RQ5 in years 2026 to 2028. First results from the study are anticipated to be published in the year 2026.

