### Attrition

Figure 3 illustrates the attrition rates by trial arms by the first data freeze in March 2025. The percentages do not accurately indicate the number of study dropouts, as all surveys are sent to participants regardless of nonresponse to previous surveys, allowing them to re-enter the study. The attrition rate has exceeded the anticipated 35% in the SPGs and TBWS. For the TBWS, the bars with black outlines represent the responses to the REDCap survey. The low response rate at the week 3 assessment (during intervention) is due to the survey only being available in REDCap and not integrated into the online course platform as in week 1 and week 7. Based on the attrition rate, we took action to increase retention, including adding incentives for the participants (a movie ticket for completing the surveys).

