Furthermore, the lack of exclusion criteria and the nonrandomized design of the protocol may introduce potential biases regarding group composition. However, allowing students to choose which intervention they participate in respects their autonomy and aligns with ethical research practices. This nonrandomized design increases the ecological validity of our findings by capturing the experiences of students in a real-world educational environment, which is important for making informed decisions that can improve services at both individual and population levels [80]. Ecological validity was further increased by including all students in the interventions and in the study. We will implement strategies to address potential selection bias, including collecting detailed demographic and baseline data and using inverse propensity score weighting using double robust estimators, if necessary.

Due to the absence of comparable previous research with the same study population, a priori sample size calculations were not conducted. This represents a limitation, as underpowered samples may fail to detect treatment effects, while overpowered samples may lead to unnecessary use of resources. Nonetheless, the existing literature indicates that significant treatment effects can be observed with smaller sample sizes in different populations [17,24]. Given the complexity of our analysis plan, which includes mixed model analyses and potential (double robust) inverse propensity score weighting, we believe it was justified to aim for a larger target sample size in this study.

We did not appoint an independent data monitoring committee, as this is a naturalistic trial without randomization, and it investigates interventions that focus on psychosocial well-being rather than alleviating psychiatric pathologies. Moreover, there were no clinical inclusion criteria, and as the participants were university students, most showed rather low levels of psychological distress. Therefore, we anticipated minimal risk of harm from the interventions, a decision that was also accepted by the ethical review board of the study. However, we recognize that the presence of such a committee could have enhanced the integrity and trustworthiness of the data collection process.

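### The 95% power quoted for small effects applies to a difference of about 0.40 to 0.46 SD; for a conventionally small effect the same test has about 27 to 53%

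*Protocol article*

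**What the plan says.** The Sample Size section sets a minimum of "600 participants, distributed evenly across 4 groups (150 participants per group") for RQ1 to RQ3. It says exact a priori calculations were not possible, then reports a G*Power estimate "on a repeated measures analysis of variance design with between-groups factors". With multiple comparisons and 35% attrition taken into account, this target "would yield at least 95% power for the detection of small effect sizes (*f*=0.20", the size label being credited to Cohen. Alpha, the number of waves, the correlation between waves and any clustering allowance are not given. The section ends by expecting the sample to be "sufficient to detect meaningful treatment effects, or lack thereof".

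Strengths and Limitations lists as a limitation that "a priori sample size calculations were not conducted". RQ1 (Aim and Objectives) compares G4H with each of the other three arms. Statistical Analyses plans linear mixed models of change over time for hierarchical data. The Results section reports: "For the SPGs, the target sample size was not attained (n=125"). It also reports: "The attrition rate has exceeded the anticipated 35% in the SPGs and TBWS".

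**The concern.** A power statement is read together with the effect size attached to it. A reader told that the trial has 95% power for small effects will treat a null result for G4H against the psychologists' groups (SPG) or the online course (TBWS) as good evidence that any difference is at most small. The closing phrase about detecting a lack of effect invites that reading. If the 95% belongs to a difference of 0.40 SD or more, a null result leaves smaller differences open. Comparisons between two active interventions are where differences below 0.40 SD are easiest to imagine.

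**Working it through.** **Inputs from the article.** 600 recruited, four arms, 35% attrition: 600 × 0.65 = 390 retained, or 97.5 per arm. ULS-8 and PHQ-9 are measured at four waves (Table 1). Group sizes are 4 to 9 (G4H), 10 to 12 (SPG) and about 5 (TBWS).

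**Assumptions, because the article gives no value.** Alpha 0.05 or 0.05/6 (all six arm pairs); correlation between waves r = 0.5, with 0.7 as a variant; m = 4 waves.

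**1. The stated figure.** For the between-groups factor, λ = f²·N·m / [1 + (m − 1)r], with 3 and N − 4 degrees of freedom.
- r = 0.5: λ = 0.04 × 390 × 4 / 2.5 = 24.96. Power is 96.2% at 0.05/6 and 99.3% at 0.05.
- r = 0.7: λ = 62.4 / 3.1 = 20.13. Power is 90% at 0.05/6 and 97.5% at 0.05.

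So at least 95% is reproduced with r = 0.5 and a six-pair correction.

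**2. What f = 0.20 means in SD units.**
- Two equal arms: f = d/2, so d = 0.40.
- One arm of four differs by δ: f = δ√(1/4 × 3/4) = 0.433δ, so δ = 0.20/0.433 = 0.46.

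The usual cut-points (0.10 small, 0.25 medium) are convention and are not printed in the article. The SD conversion does not depend on them.

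**3. The same test at f = 0.10.** λ = 0.01 × 390 × 4 / 2.5 = 6.24. Power is 53% at 0.05 and 27.5% at 0.05/6.

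**4. G4H against one other arm, 97.5 per arm.** SE = √(v × 2/97.5), where v is the residual variance in SD² units.

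| Contrast | v | SE | d = 0.40, alpha 0.05 / 0.05/6 | d = 0.20, alpha 0.05 / 0.05/6 |
|---|---|---|---|---|
| One follow-up, unadjusted | 1 | 0.143 | 79% / 55% | 29% / 11% |
| One follow-up, baseline r = 0.6 | 1 − 0.36 = 0.64 | 0.115 | 94% / 79% | 41% / 18% |
| Mean of three follow-ups, baseline-adjusted, r = 0.5 | (1 + 2 × 0.5)/3 − 0.25 = 0.417 | 0.092 | 99% / 95% | 58% / 31% |

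**5. Group delivery.** Assume an ICC of 0.05 and group sizes of 6.5, 11 and 5, with controls unclustered. The arm design effects, 1 + (n − 1) × 0.05, are 1.275, 1.5, 1.2 and 1. Effective numbers: 97.5/1.275 + 97.5/1.5 + 97.5/1.2 + 97.5 = 320, so the overall factor is 390/320 = 1.22. Omnibus power at f = 0.20 and alpha 0.05/6 becomes about 91% (r = 0.5) or 81% (r = 0.7). At an ICC of 0.02 the factor is 1.09 and power is 94% or 86%.

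**6. Detectable difference from recruited numbers.** G4H: 155 × 0.65 = 100.75. SPG: 125 × 0.65 = 81.25, an upper figure because SPG attrition exceeded 35%. SE = √(1/100.75 + 1/81.25) = 0.149. At one visit, 80% power and alpha 0.05: 2.80 × 0.149 = 0.42 SD unadjusted, or 0.42 × √0.64 = 0.33 SD with baseline r = 0.6. Neither figure allows for clustering.

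**The case against.** The case for leaving the section alone has several parts.

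**The arithmetic is sound, and the section calls it an estimate.** Both are true. A reader might infer a calculation error; step 1 shows there is none. The error lies in the label and in what is concluded from it.

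**The omnibus main effect is inferred.** The named design points to it, but the article does not rule out a group-by-time interaction, which at f = 0.20 would also exceed 95%. One cannot therefore say that the figure arises only as a main effect averaging in baseline. The interaction reading does not rescue the label. If one arm differs by d at all three later waves, f = d × 3/16, so even f = 0.10 means d = 0.53. A difference of 0.20 SD would have 8 to 25% power (r = 0.5).

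**The arm contrasts are not generally underpowered.** A reader might infer that power collapses once arms are compared in pairs. At 0.40 SD it does not: the planned mixed models use all waves, and the averaged, adjusted contrast keeps 95 to 99%. The losses come at 0.20 SD, at a single visit (especially with a corrected alpha), or with clustering.

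**Recruitment went well overall.** In total 699 students joined, with 155, 216 and 203 in G4H, TBWS and controls; only SPG fell short. The mixed models will also use students with partial follow-up, so a 35% loss is somewhat pessimistic for them. Both points stand, and neither changes what f = 0.20 means.

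**The earlier trials support the sample size.** One might turn this round, since those trials required low mood and loneliness, and one found depression reduced in both arms "with no significant differences between G4H and CBT". But that trial also reported that the loneliness reduction was maintained with G4H, and the article already says that the earlier designs and populations differ. This comparison carries no weight in the conclusion.

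**The limitations section already warns about underpowered samples.** It does, but the 95% claim stands uncorrected beside that warning.

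**Conclusion.** The concern holds as an error of labelling and interpretation. The stated 95% is power for a difference of about 0.40 to 0.46 SD. For a conventionally small effect (f = 0.10) the same test has about 27 to 53%. For G4H against one arm, 0.40 SD is well covered by an averaged, baseline-adjusted contrast (95 to 99%) and less well at one follow-up (55 to 79% unadjusted, 79 to 94% with baseline r = 0.6). At 0.20 SD a single-visit contrast has only 11 to 41%. These figures rest on assumed alpha (0.05 to 0.05/6), r = 0.5 between waves, and independent students. An assumed ICC of 0.05 takes the omnibus figure at f = 0.20 to about 91%, or 81% if r is 0.7, both at 0.05/6.

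A reader might go further and infer that the sample is too small or that more students are needed. The documents do not support that: they fix no smallest difference of interest, and the target was met in three of four arms. What they cannot support is reading a null pairwise result as a lack of effect on the strength of this power figure.

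**What to change.** In Sample Size:
- Drop the word small. State about 96% omnibus power for f = 0.20 (0.40 to 0.46 SD), naming the alpha, correlation, number of waves and independence assumption actually entered in G*Power. If those inputs differ from the ones assumed here, report the figure they give.
- Add that power at f = 0.10 is about 27 to 53%.
- Give the detectable difference for G4H against each other arm from retained numbers. For SPG at one visit this is about 0.42 SD unadjusted, or 0.33 SD with baseline r = 0.6, before clustering. Say that group delivery widens it.
- Delete the words claiming that a lack of treatment effect could be detected.

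Then make this section agree with Strengths and Limitations, for example by saying in both places that an approximate power estimate was made without trial-specific inputs.

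The cost is a few sentences and a less favourable headline figure. Enrolment and the planned analysis do not change.
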